# Sustained inflations versus UK standard inflations during initial resuscitation of prematurely born infants in the delivery room: a study protocol for a randomised controlled trial

**DOI:** 10.1186/s13063-017-2311-y

**Published:** 2017-11-28

**Keywords:** Resuscitation, Sustained inflation, Prematurely born infants

## Abstract

**Background:**

Many infants born at less than 34 weeks of gestational age will require resuscitation in the delivery suite. Yet, different resuscitation techniques are specified in different national guidelines, likely reflecting a limited evidence base. One difference is the length of mechanical inflation initially delivered to infants either via a facemask or endotracheal tube. Some guidelines specify short inflations delivered at rates of 40–60/min, others recommend initial inflations lasting 2–3 s or sustained inflations lasting for ≥ 5 s for initial resuscitation. Research has shown that tidal volumes > 2.2 mL/kg (the anatomical dead space) are seldom generated unless the infant’s respiratory effort coincides with an inflation (active inflation). When inflations lasting 1–3 s were used, the time to the first active inflation was inversely proportional to the inflation time. This trial investigates whether a sustained inflation or repeated shorter inflations is more effective in stimulating the first active inflation.

**Methods:**

This non-blinded, randomised controlled trial performed at a single tertiary neonatal unit is recruiting 40 infants born at < 34 weeks of gestational age. A 15-s sustained inflation is being compared to five repeated inflations of 2–3 s during the resuscitation at delivery. A respiratory function monitor is used to record airway pressure, flow, expiratory tidal volume and end tidal carbon dioxide (ETCO_2_) levels. The study is performed as emergency research without prior consent and was approved by the NHS London-Riverside Research Ethics Committee. The primary outcome is the minute volume in the first minute of resuscitation with secondary outcomes of the time to the first active inflation and ETCO_2_ level during the first minute of recorded resuscitation.

**Discussion:**

This is the first study to compare a sustained inflation to the current UK practice of five initial inflations of 2–3 s.

**Trial registration:**

ClinicalTrials.gov, NCT02967562. Registered on 15 November 2016.

**Electronic supplementary material:**

The online version of this article (doi:10.1186/s13063-017-2311-y) contains supplementary material, which is available to authorized users.

## Background

Seventy-five percent of infants born at < 34 weeks of gestational age require resuscitation including positive pressure ventilation and/or endotracheal intubation at delivery [1]. Current UK guidelines recommend initial resuscitation using five inflations of 2–3 s duration with peak inflation pressures of 20–25 cmH_2_O [2]. It has been shown, however, that despite resuscitation training, clinicians in both simulated and real resuscitation scenarios do not deliver the recommended duration of the inflations [3, 4]. This, combined with leaks around the facemask often as large as 50% or greater, contributes to low expired tidal volumes during resuscitation [5]. Indeed, during resuscitation by facemask or endotracheal tube, tidal volumes and end tidal carbon dioxide (ETCO_2_) levels remained low until a respiratory effort was made coinciding with a mechanical inflation (an active inflation) [3, 6]. Analysis of data collected during the resuscitation of infants born at < 34 weeks of gestational age who received inflations of 1–3 s in duration demonstrated that active inflations occurred sooner with longer inflation times [7].

There is evidence that sustained inflations (≥5 s) may be of benefit. In preterm rabbits, a sustained inflation of 20 s compared to a shorter inflation or no inflation before mechanical ventilation was commenced was associated with a more rapid establishment of a functional residual capacity; 90% of lung aeration was achieved within the first 14 s [8, 9]. Preterm lambs who received a 60-s sustained inflation followed by mechanical ventilation compared to those who received ventilation alone (tidal volumes of 7 mL/kg delivered at a rate of 60 bpm) had increased pulmonary blood flow, more stable cerebral oxygen delivery and better compliance during subsequent ventilation [10]. Comparison of five repeated 3-s inflations to a 20-s sustained inflation in asphyxiated lambs delivered near term showed that the sustained inflation provoked an earlier rise in heart rate, improved gas exchange and improved lung compliance during subsequent ventilation [11]. Another study in lambs, however, showed that a 30-s sustained inflation compared to no sustained inflation led to more cerebral vascular leakage and potential perturbation of blood–brain barrier function [12]. In all of the above studies, the lambs were sedated during resuscitation, whereas infants are not and indeed their respiratory efforts can make an important contribution to gas exchange [3, 6].

There have been several studies of sustained inflations in infants. Early studies in term infants born after elective Caesarean section demonstrated that a 5-s inflation produced a larger inflation volume than a 1-s inflation and also was more efficient at establishing a functional residual capacity [13, 14]. A study of infants born at < 32 weeks of gestational age demonstrated that those who were resuscitated with a sustained inflation compared to a historical cohort resuscitated without a sustained inflation were less likely to be intubated (51% vs 76%, *p* < 0.0001) and had lower durations of mechanical ventilation (5 vs 11 days, *p* < 0.008) and supplementary oxygen therapy (21 vs 31 days, *p* = 0.016) [15]. They were also less likely to receive postnatal steroids (25% vs 10%, *p* = 0.01) and had a lower incidence of bronchopulmonary dysplasia (BPD) (7% vs 25%, *p* = 0.04) [15]. Another study compared infants born at < 34 weeks of gestational age who received a 15-s sustained inflation to a historical cohort who received recurrent inflations at 60 breaths per minute. The sustained inflation group had a lower need for intubation (6% vs 21%, *p* < 0.01) and a shorter duration of ventilation (9.1 vs 13.8 days, *p* < 0.001) [16]. The findings of both studies [15, 16], however, should be interpreted with caution as other changes in perinatal care may have influenced the outcomes. In infants born at 25–33 weeks, a 10-s sustained inflation delivered via a nasopharyngeal tube compared to ventilation with initial inflation pressures of 30–40 cmH_2_O, then 20 cmH_2_O, at a rate of 60 bpm via a bag-mask device, was associated with a lower need for endotracheal intubation and mechanical ventilation, a shorter duration of total respiratory support and a lower rate of BPD. There were, however, limitations to the study, as the ‘ventilation’ group did not receive positive end expiratory pressure (PEEP) during resuscitation and were intubated and ventilated after 30 s of mask ventilation if unstable, whereas the sustained inflation group subsequently received nasal continuous positive airways pressure (CPAP) or several minutes of nasal ventilation as part of stabilization [17]. A randomised trial comparing a 15-s sustained inflation to resuscitation with inflations at 60 breaths per minute both delivered by nasopharyngeal tube, did not demonstrate significant differences in the need for mechanical ventilation. The trial, however, was stopped early due to slow recruitment [18]. In a subsequent randomised trial enrolling infants born at 25–29 weeks of gestational age, a 15-s sustained inflation followed by nasal CPAP was compared to nasal CPAP alone. A smaller proportion of the sustained inflation group required mechanical ventilation in the first 72 h after birth (53% vs 65%, *p* = 0.04) [19]. A further randomised trial enrolled infants born at 25–32 weeks of gestational age and randomised them to either a 15-s inflation at 25 cmH_2_O or resuscitation as per the American Heart Association guidelines (positive pressure ventilation at 15–20/5 cmH_2_O). A lower inspired oxygen concentration (FiO_2_) 10 min after delivery was demonstrated in the sustained inflation group (0.28 vs 0.47) (*p* < 0.01). Among those born < 28 weeks of gestational age, there was a lower need for intubation in the group that received a sustained inflation (29% vs 63%, *p* = 0.05), but this was not a pre-specified analysis [20]. In contrast to those promising results in moderately or extremely prematurely born infants, in infants born at 34–36 weeks of gestational age there were no significant differences in the need for respiratory support, the incidence of neonatal intensive care unit (NICU) admission for respiratory distress or the total length of NICU stay between infants who received a 15-s sustained inflation and those who received standard resuscitation according to the American Association of Pediatrics guidelines (drying, stimulation and, if inadequate respiratory effort or a heart rate < 100 bpm, positive pressure ventilation at 40–60 inflations per minute) [21].

There have been concerns raised regarding potential adverse effects of sustained inflations, in particular relating to air leak, intraventricular haemorrhage (IVH) and patent ductus arteriosus [22, 23]. Non-significant increases in IVH in infants born at < 28 weeks of gestational age [16] and non-significant increases in pneumothorax in infants born at < 34 weeks of gestational age have been reported in those exposed to sustained inflations [19]. A meta-analysis of four small trials [24], however, showed no significant differences in rates of pneumothorax or of IVH. A subsequent study of prematurely born infants showed a non-significant decrease in pneumothorax with a 15-s sustained inflation compared to ventilation with a self-inflating bag [25]. The peak inspiratory pressures, however, used in the bag-mask ventilation were up to 40 cmH_2_O, whereas those used in the sustained inflation group were 30 cmH_2_O [25]. The meta-analysis [24] also reported that in the sustained inflation group there was a higher proportion of infants who required treatment (medical or surgical) for a patent ductus arteriosus (relative risk = 1.27 [95% confidence interval = 1.05–1.54]). Cerebral blood flow, as assessed by near-infrared spectroscopy, however, was more stable in preterm infants resuscitated with a sustained inflation compared to in those who were resuscitated without a sustained inflation [26–28]. In addition, in prematurely born infants, a 5-s inflation compared to a 2-s inflation was not associated with higher levels of inflammatory cytokines (IL-6, IL-10, IL-1β, and TNF-α) in bronchoalveolar fluid [29].

Resuscitation guidelines from the USA, UK and Europe suggest that sustained inflations should be researched further [30, 31]. To date, there are no studies comparing sustained inflations to the current UK practice of the first five inflations lasting 2–3 s. In addition, there has only been one study in which a respiratory function monitor was used to assess the physiological effects of a sustained inflation. Sustained inflations were shown not to be effective in producing tidal volumes > 2.5 mL/kg or generating a functional residual capacity unless there was spontaneous respiratory effort during the inflation, but there was no comparison to other methods of resuscitation [32]. The aim of this study, therefore, is to determine whether a 15-s sustained inflation or five inflations each of 2–3 s duration is more effective at stimulating respiratory efforts in prematurely born infants. The primary outcome is the minute volume in the first minute of resuscitation and the secondary outcomes are the time to the first active inflation (inspiration occurring during an inflation) and end tidal carbon dioxide (ETCO_2_) levels in the first minute.

## Methods

This is a non-blinded, randomised superiority trial. Infants are allocated to parallel groups in a 1:1 ratio.

### Setting

A single tertiary neonatal unit at King’s College Hospital, London, UK

### Inclusion criteria

Inclusion criteria are as follows:Infants delivered at < 34 weeks of gestational age.The clinical team present before delivery and trained both in the use of the respiratory function monitor and to deliver sustained inflations.

### Exclusion criteria

Major congenital abnormalitiesRefusal of consent for the data to be analysed (see later).

### Recruitment

This study is conducted as emergency research without prior consent. As soon as possible after delivery, parents are approached to inform them about the study and to ask them for written, informed consent for retention and analysis of the respiratory function data. The study and this retrospective consent approach were approved by the Health Research Authority and by the London-Riverside NHS Research Ethics Committee. Posters giving information about the study are displayed in the antenatal ward and on the delivery suite, and parents of eligible infants are encouraged to contact the researchers before delivery if they would like to discuss the study.

### Randomisation

The randomisation sequence is generated using a computerised random number generator and concealed in sealed, opaque envelopes. This is done by a person independent of the research team who is not involved in the study.

### Enrolment

Infants will be enrolled in the study by the clinical team attending the delivery. Infants will be deemed to be enrolled if the monitoring equipment is taken to the delivery, the infant is randomised into the study by opening the next envelope, and they do indeed require stabilisation.

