### Blinding

The study is not blinded. Decisions regarding ongoing care, for example, the need for intubation and mechanical ventilation are made by the clinical team alone according to the unit’s guidelines.

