### Intervention

At delivery, eligible infants are randomised either to receive five inflations each of 2–3 s duration as per the current UK Neonatal Life Support guidelines [2] or a 15-s sustained inflation (Fig. 1). Resuscitation is performed using a t-piece device (Neopuff Infant Resuscitator, Fisher & Paykel Healthcare, Auckland, New Zealand). Both the sustained inflation and the five 2–3 s inflations are performed using a peak inspiratory pressure of 25 cmH_2_O and PEEP of 5 cm H_2_O as per unit guidelines. As per unit guidelines, PEEP of 5 cmH_2_O is provided between inflations and between sets of inflations. Either the sustained inflations or the five inflation breaths may be repeated once and, if the baby is initially resuscitated by facemask and subsequently intubated, the sustained inflations or five 2–3 s inflations as per randomisation may be repeated twice if necessary. All trainees are trained to deliver the sustained inflation on a mannequin and using the respiratory function monitoring equipment.

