### Primary outcome measure

The primary outcome measure is the minute volume in the first minute of ventilation

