### Statistical analysis

Analysis will be conducted on an intention-to-treat basis. The data will be assessed for normality and if found not to have a normal distribution, non-parametric statistics will be used to assess if there are any significant differences in outcomes between the two groups. Analysis will be undertaken using IBM SPSS Statistics for Windows, version 22.

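### The enrolment rule appears to let an unblinded team exclude infants after randomisation, which does not fit the 40 randomised or the intention-to-treat promise

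*Protocol article*

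**What the plan says.** All references are to the protocol article.

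- **Enrolment.** "Infants will be enrolled in the study by the clinical team attending the delivery". Three conditions must hold together. The monitoring equipment is at the delivery, and "the infant is randomised into the study by opening the next envelope, and they do indeed require stabilisation".
- **Inclusion criteria.** There are two: "Infants delivered at < 34 weeks of gestational age", and "The clinical team present before delivery and trained both in the use of the respiratory function monitor and to deliver sustained inflations". Need for stabilisation is not one of them.
- **Intervention.** "At delivery, eligible infants are randomised either to receive five inflations" or the single 15-s inflation. The section does not say that need is confirmed before the envelope is opened.
- **Blinding.** "The study is not blinded".
- **Sample size.** The power statement is tied to 40 infants being randomised.
- **Statistical analysis.** "Analysis will be conducted on an intention-to-treat basis". The section does not say whether this covers all randomised or only enrolled infants.
- **Exclusion criteria.** Parental refusal of data use is a further exclusion. Under deferred consent it also falls after randomisation.

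**The concern.** If need is a condition separate from opening the envelope, an infant can be randomised and then not count. The people who decide are the attending team, and nothing in the article stops them from knowing the arm when they decide. The article states no criterion for needing stabilisation.

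The primary outcome makes this sensitive. It is minute volume in the first minute of ventilation, and the Background explains that tidal volumes stay low until the infant makes a respiratory effort during an inflation. Infants who are already partly breathing are plausibly those whose need is most open to debate and also those with the largest volumes. If a team about to give one long inflation judged such infants differently from a team about to give five short ones, the two groups would differ in vigour before any treatment effect. Sealed opaque envelopes protect the allocation up to opening, but not against exclusions made afterwards.

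There is also a plain cost in numbers. If 40 means randomised, any exclusion leaves fewer than 40 in the analysis.

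**Working it through.** **1. The plan's own figure.** Inputs from Sample size: SD 71, difference 71 mL/min/kg, 5% level (taken as two-sided), 40 infants. With 1:1 allocation (Methods) that is 20 per arm. Normal approximation:

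power = Φ(√(n/2) × difference/SD − 1.96) = Φ(√10 × 1 − 1.96) = Φ(1.202) = 88.5%.

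This is close to the stated 90%. The t-test gives 86.9%. The defect does not come from this figure.

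**2. Loss of power if 40 are randomised and some are dropped.** The Background gives 75% as the share of infants below 34 weeks who need resuscitation. Assume that share also applies to stabilisation. Then 40 × 0.75 = 30 remain, 15 per arm:

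power = Φ(√7.5 − 1.96) = Φ(0.779) = 78.2% (t-test 75.3%).

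With smaller losses, by the normal approximation:
- 5% dropped: 86.9%
- 10% dropped: 85.1%
- 20% dropped: 80.7%

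If 40 instead means enrolled, power stays at 88.5%. At the same 25% loss, about 40/0.75 = 53.3, so 54 envelopes, would have to be opened.

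**3. Possible bias.** The documents give no figure for this, so every input except the SD is an assumption. Suppose that vigour is normally distributed, that it has correlation r with minute volume (0.3 to 0.7), that the most vigorous fraction q is dropped in each arm, and that 20 per arm are analysed with SD held at 71. Mean vigour among those kept is

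m(q) = −φ(z₁₋q)/(1−q),

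and the spurious difference is r × 71 × [m(q₁) − m(q₂)]. The arm that drops more looks worse.

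Example, 30% v 20%: m(0.30) = −0.3477/0.70 = −0.497 and m(0.20) = −0.2800/0.80 = −0.350, a gap of 0.147. Then 0.3 × 71 × 0.147 = 3.1 and 0.7 × 71 × 0.147 = 7.3 mL/min/kg.

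The type I error uses SE = 71 × √(1/20 + 1/20) = 22.5.

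| Dropped, arm 1 v arm 2 | Gap in mean vigour | Spurious difference, r = 0.3 to 0.7 | Two-sided type I error |
|---|---|---|---|
| 25% v 25% | 0 | 0 | 5.0% |
| 30% v 20% | 0.147 | 3.1 to 7.3 | 5.2% to 6.2% |
| 35% v 15% | 0.296 | 6.3 to 14.7 | 5.9% to 10.0% |
| 40% v 10% | 0.449 | 9.6 to 22.3 | 7.1% to 16.9% |

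Against the target of 71, the range from 3.1 to 22.3 is 4% to 31%.

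**4. The sections side by side.** Eligibility does not mention need. Enrolment requires it in addition to randomisation. Sample size counts the randomised. Statistical analysis promises intention-to-treat. All four can hold together only if need is always settled before the envelope is opened, and the article does not say so.

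**The case against.** The strongest objection concerns sequence. The Enrolment section lists conditions that must all hold and gives no order in time. The trial flowchart, the likeliest place to show the order, is not available to this review. A reader might infer that the envelope is always opened before need is known. The text does not establish that. It does point that way: a separate condition of need would be redundant if need were already settled at opening, and the wording suggests later confirmation. That supports saying the rule appears to allow such exclusions, and no more.

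Second, a reader might infer that the analysis flatly breaks intention-to-treat. That goes too far. "The primary outcome measure is the minute volume in the first minute of ventilation", so the outcome does not exist for an infant who is never ventilated, and some restriction to ventilated infants is unavoidable. The article also leaves open which set the term covers, and detailed analysis sets may be defined in a plan not shown here. What stands is that the restriction appears able to fall after allocation, in the hands of an unblinded team.

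Third, the judgement of need may follow national or unit guidance whose criteria are not shown, so it cannot be called purely subjective.

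Fourth, the 25% complement comes from a background figure for resuscitation. Stabilisation is not defined and may be broader, so the number dropped could be much smaller.

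**Conclusion.** The point holds as a flaw in how enrolment is fixed: as worded, randomised infants can apparently be excluded by staff who can know the arm, and the article does not reconcile this with 40 randomised or with intention-to-treat.

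A reader might go on to infer that the comparison is biased, or that randomisation no longer protects it. The documents do not support that. If need is judged independently of arm there is no bias, and the only cost is power. If it is not, the direction is unknown. The size depends wholly on assumed differences in dropping and an assumed correlation of vigour with minute volume. The figure of 22 mL/min/kg is the extreme of the range examined.

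The fall in power to about 78% rests on two readings: that 40 means randomised, and that the Background's 75% applies to stabilisation.

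The point still deserves action, because nothing in the article secures independence from the arm, and because relabelling the analysis set would not remove the risk.

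**What to change.** - **Order.** Make the team's declaration that inflations are needed the last inclusion criterion, and open the envelope only after it. Both arms use the same T-piece at the same pressures (Intervention), so the article shows nothing arm-specific that must be prepared earlier.
- **Analysis set.** Define intention-to-treat as every infant randomised at that point, less parental refusals of data use, with the refusals reported by arm.
- **Reconcile.** Align Inclusion criteria, Enrolment, Sample size and Statistical analysis on whether 40 means randomised or enrolled.
- **Infants already randomised.** Report every opened envelope by arm with the reason for any non-inclusion, and call that set modified intention-to-treat.

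The cost is an amendment, a staff briefing and one extra step at the resuscitation station. The trial was already recruiting when the article was submitted, so infants will have been enrolled under two rules. Results from before and after the change should be identified as such. If the practice already follows this order, the remedy is a clarifying sentence.
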